## Abstract

**Background:**

Psychological interventions may reduce fertility problems. Positive emotion, engagement, meaning, positive relationship and accomplishment (PERMA) is a cognitive intervention and integrative-behavioral couple therapy (IBCT) is a behavioral intervention. Appropriate mental interventions are important in infertility treatment.

**Objective:**

To investigate the effect of the PERMA model vs. IBCT in reducing the fertility problems of couples.

**Materials and Methods:**

The content of the interventions was developed and adjusted based on a literature review and the opinions of experts. In this three-arm parallel randomized clinical trial, 42 couples undergoing infertility treatment will be allocated randomly into three groups (n = 14 couples/each). Group 1 will receive the PERMA intervention, group 2 will receive the IBCT intervention, and group 3 as the control group will receive an infertility treatment training program intervention. The primary outcome will be the fertility problems, which will be measured by completing a fertility problem inventory at baseline, as well as in the 5
${}^{\text{th}}$
 and 9
${}^{\text{th}}$
 wk as a follow-up. Another primary outcome, satisfaction with the intervention, will also be assessed in the 5
${}^{\text{th}}$
 and 9
${}^{\text{th}}$
 wk. The secondry outcome will be a positive pregnancy test at wk 12. The interventions will be conducted through a combination of face-to-face and online via WhatsApp.

**Conclusion:**

This study will assess social, sexual, and parenthood concerns. A combination of online and face-to-face interventions will be appropriate given the COVID-19 pandemic. Couple's counseling may provide better counseling outcomes for fertility problems in comparison with group counseling. This study will try to optimize resilience during infertility treatment through learning better relationship and problem-solving skills, and may have an indirect impact on pregnancy rate, burden of infertility, and costs of treatment due to increased effectiveness.

## 1. Introduction 

Infertility is defined as the absence of pregnancy following a year of regular sexual intercourse (without the use of contraception) (1). The fertility problem inventory (FPI) measures perceived infertility-related stress and specific domains of patient concern. Worldwide prevalence of primary infertility is about 12-15%. According to Sun and colleagues, from 1990 to 2017, the prevalence of primary infertility increased to 14.9% in women and 8.2% in men (2). In another study, infertility prevalence was reported as nearly 13.2% in Iran (3).

Infertility treatments, from medical monitoring to fertilization procedures, impose a severe physical and psychological burden on women and their husbands (4). Women undergoing infertility treatments report higher levels of stress, anxiety, and depression, which affect their quality of life, marital relationships, and sexual functioning. They may experience various psychological problems, such as low self-esteem, anger, sadness, anxiety, and jealousy towards other couples who have children. Fear of childbirth may develop in women who have more extended anxiety during infertility treatment, which may lead to more pregnancy complications and operative deliveries in comparison with women who conceive naturally, because of the effect of fear on unsuitable cervical ripening and preparation for vaginal delivery (5, 6).

For these reasons psychological counseling and interventions are necessary. Psychological intervention can relieve the patients' stress, depression, and fatigue, facilitate marital intimacy, and promote sexual satisfaction (7). Due to the outbreak of COVID-19 and the necessity to comply with social distancing, mental disorders in this group have increased. Nowadays, using new online telecommunication software instead of face-to-face counseling can reduce the psychological problems of couples with infertility (8).

Different infertility treatment problems, such as costs, complexities and complications of medical treatments can activate body stressors. Cortisol has a negative effect on infertility (9). In contrast, having a positive mood is beneficial on cardiovascular function including heart rate and blood pressure, and also on the immune system, which can be associated with better fertility outcomes (9, 10).

Psychological counseling interventions may be effective in decreasing fertility problems by providing skills for couples to manage their stress during infertility treatment (11). One of these cognitive interventions that can be used is a positive-oriented intervention which includes elements focusing on: 1) positive emotions; 2) engagement; 3) relationship; 4) meaning; and 5) accomplishment. This is called the PERMA model and it is based on Seligman's PERMA theory of well-being (12-15). Behavioral approaches can also be used for infertile couples' therapy. One such model is integrative-behavioral couple therapy (IBCT) (16). This approach is primarily focused on strategies to promote emotional acceptance in relationships. These strategies focus on feeling empathy, showing tolerance for problems, gaining problem-solving skills and changing the couple's behavior (17). Many couples undergoing infertility treatment are not fully aware of the treatment process and they complain about this issue. This informational gap might lead to anxiety. Provision of information regarding infertility treatment methods can help to reduce anxiety among couples undergoing infertility treatment (18).

Although some studies have been conducted regarding fertility problems (7, 19), our approach is novel in comparing three different counseling methods, including a positive-oriented therapy (PERMA, focusing on increasing good mood), couple's therapy (IBCT, focusing on enhancement of the couple
${}^{{}^{'}}$
s relationship), and an infertility treatment training program, using new online telecommunication software, plus face-to-face counseling. Since cognitive and behavioral approaches are both common for psychological counseling in cases of infertility treatment (11), both were included in the study.

This study will aim to compare the effectiveness of the PERMA model vs. IBCT in reducing the fertility problems of couples undergoing infertility treatment.

## 2. Materials and Methods

This randomized clinical trial will be conducted in 2021. The primary objects of study will be a comparison of the effectiveness of the PERMA model vs. IBCT on reducing the fertility problems of couples undergoing infertility treatment, and satisfaction with the interventional methods.

### Objects

The primary object is determining and comparing the mean scores of fertility problems in women, men and couples at the baseline of the intervention, at the end of the 5
${}^{\text{th}}$
 wk of the intervention, and one month after ending the intervention (in the 9
${}^{\text{th}}$
 wk) in the three study groups. The other primary outcome will be the mean satisfaction scores of the interventional method in women, men and couples at the end of the 5
${}^{\text{th}}$
 wk of the intervention and one month after the intervention (in the 9
${}^{\text{th}}$
 wk) in the three study groups. The secondary outcomes will be the frequency and percentage of pregnancy at the time of follow-up (in the 12
${}^{\text{th}}$
 wk) in the three study groups (Figure 1).

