### Sampling and sample size

The estimated sample size is 84 husbands and wives (14 couples in each group) based on a previous study (23) and considering α = 0.05, β = 90%, power = 80% and σ = 2.5, and 15% attrition rate. The statistical formula used for sample size determination was n = 2 (z 1-
α
 / 2 + z 1 -
β
)^2^

σ

^2^ / (µ1-µ2)^2^.

In this three-arm parallel randomized clinical trial, two intervention groups (the PERMA model and IBCT) and a control group (infertility treatment training program) will be studied. 42 couples will be allocated into the three groups randomly (14 in each). Written and verbal informed consent will be obtained from husbands and wives separately.

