### Statistical analysis

Frequency, percentage, mean, and standard deviation will be used to measure descriptive data. Shapiro-Wilk's normality test will be applied to determine the normal distribution of quantitative data. Chi-square test will be done for comparing qualitative data. Parametric analytic statistical tests like ANOVA will be applied for the measurement of the two primary outcomes (fertility problems and satisfaction with the intervention method) if the data have a normal distribution. P-values 
<
 0.05 will be considered significant.

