## 4. Conclusion

This study will assess social, sexual, relationship and parenthood concerns. A combination of online and face-to-face interventions is appropriate for times of COVID-19 outbreaks. Couple's counseling may provide better outcomes for fertility problems in comparison with group counseling. A package for intervention sessions will be provided and the effectiveness of two psychological interventions (PERMA and IBCT) will be compared with the control group. This study will try to optimize resilience during infertility treatment through learning better relationship and problem-solving skills, which may also have an indirect impact on pregnancy rate, burden of infertility, and costs of treatment due to increased effectiveness.

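### Two primary outcomes, each in three populations at two follow-up times, share a flat 0.05 with no lead endpoint, and the arm contrast of interest differs between sections

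*Protocol article*

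**What the plan says.** **Endpoints.** The Objects section of the protocol article names FPI as primary, compared in women, men and couples at baseline, week 5 and week 9 across the three groups. It then adds: "The other primary outcome will be the mean satisfaction scores of the interventional method in women, men and couples", at weeks 5 and 9. The Outcomes section repeats the same structure, and the abstract also calls both outcomes primary.

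**Test and threshold.** The Statistical analysis section plans parametric tests of the ANOVA type for both primary outcomes if the data are normal. Its only decision rule is a P-value limit: "0.05 will be considered significant". It gives no order, alpha split or lead endpoint.

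**Arm contrast.** Three versions appear:
- PERMA versus IBCT in the abstract's objective ("To investigate the effect of the PERMA model vs. IBCT in reducing the fertility problems of couples"), in the aim that closes the Introduction, and in the opening paragraph of Materials and Methods.
- All three groups in Objects and Outcomes.
- Each intervention against control in section 4, Conclusion: "the effectiveness of two psychological interventions (PERMA and IBCT) will be compared with the control group".

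**Sample size.** Sampling and sample size plans 14 couples per arm, 84 persons in all, and cites an earlier study as the source. The inputs it lists are: "considering α = 0.05, β = 90%, power = 80% and σ = 2.5, and 15% attrition rate". The formula is the usual one for two means, two-sided. No value is given for µ1−µ2, and the section does not say which outcome, population, time or pair of arms σ = 2.5 refers to.

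**The concern.** A primary endpoint is meant to settle in advance which result decides the trial. Here two outcomes, three populations and two times all carry that status at the same threshold, so a significant result in any one of them could be reported as a positive primary finding. With 14 couples per arm, a chance result in one cell is a real prospect, and the Discussion foresees use of the results in Health Ministry policy.

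The shifting contrast adds to this. A three-group ANOVA tests whether the arms differ somewhere. By itself it does not say whether PERMA differs from IBCT, or whether either differs from control. The reader cannot tell which of these the trial was designed to answer, nor to which one the stated power belongs.

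**Working it through.** **1. The plan's own sample size.** Formula: n = 2(z₁₋α/₂ + z₁₋β)²σ²/(µ1−µ2)². Inputs from Sampling and sample size: α = 0.05, σ = 2.5, attrition 15%, 14 couples per arm. The figure of 14 cannot be reproduced, because µ1−µ2 is missing and the two statements about β and power conflict (power = 1 − β, so β = 90% would mean 10% power).

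Solving backwards: 14 × 0.85 = 11.9, so about 12 evaluable couples per arm.
- At 80% power: µ1−µ2 = 2.5 × √(2/12) × (1.960 + 0.842) ≈ 2.86, or 1.14 SD.
- At 90% power: 2.5 × √(2/12) × (1.960 + 1.282) ≈ 3.31, or 1.32 SD.

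These differences are inferred, not stated. In either case α enters whole, for one two-group comparison.

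**2. Size of the primary family.** 2 outcomes × 3 populations × 2 follow-up times = 12 three-group tests, if each is tested separately. If the two times are combined in one test, 2 × 3 = 6.

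**3. Chance of at least one false positive.** With independent tests this is 1 − 0.95¹² = 46.0% for 12 and 1 − 0.95⁶ = 26.5% for 6. Both are too high for this trial, because spouses' scores, repeated scores and the couple score are related. A simulation with no true effect allows for this. The article gives no correlations and does not define the couple score, so these are assumptions: normal data, couple score = mean of the two spouses, and correlations as shown.

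| Primary tests | Couples per arm | Assumed correlations (spouse / time / outcome) | At least one P < 0.05 |
|---|---|---|---|
| 12 ANOVAs | 14 | 0.3–0.6 / 0.5–0.8 / 0–0.3 | about 26–35% |
| 6 ANOVAs, weeks 5 and 9 averaged | 14 | same | about 17–21% |
| 12 ANOVAs | 12 | from 0.7 / 0.8 / 0.5 to all zero | 24–40% |
| 6 FPI ANOVAs only | 12 | same as the row above | 14–22% |
| PERMA vs IBCT only, 12 endpoints | 12 | same as the row above | 23–39% |

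No scenario comes near 5%. Dropping satisfaction, or accepting PERMA versus IBCT as the only contrast, does not remove the excess.

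**4. What the stated power covers.** Take the back-solved difference for 80% power and 12 evaluable couples per arm. By the normal formula, power at level α/k is Φ(2.802 − z₁₋α/₍₂ₖ₎).
- k = 1: Φ(2.802 − 1.960) = 80%.
- k = 3 (three pairwise contrasts, Bonferroni): Φ(2.802 − 2.394) = 66%.
- k = 12: Φ(2.802 − 2.865) = 48%.

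If 90% was the intended power, the same three figures are 90%, 80% and 65%. On a t-test basis with the 80% difference, power starts at 76% and falls to 59% for k = 3. These figures are illustrative, since the difference itself is inferred.

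**The case against.** **A lead contrast is named.** A reader might infer that the plan has no lead comparison at all. That is too strong. The abstract, the Introduction and the opening of Materials and Methods all give PERMA versus IBCT. The fault is that Objects, Statistical analysis and Conclusion do not follow it.

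**Pairwise tests are not in the plan.** It is tempting to multiply the 12 tests by three pairs of arms and count 36 contrasts at 0.05. Unprotected, these would give at least one false positive in about 49–72% of null trials. The article states no pairwise tests, however, and post-hoc procedure is commonly left to a fuller document. With exactly three arms, pairwise tests made only after a significant ANOVA hold each endpoint at 5%, and the family figure stays at 26–35%.

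**Twelve separate ANOVAs is one reading.** The wording on tests does not exclude a repeated-measures model, which could merge the times. This stands, and is why the 17–21% figure is given alongside.

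**ANOVA does answer one stated question.** The Introduction and Objects also speak of comparing three groups, and an omnibus test addresses that. It does not address the pairwise aim that the objective states.

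**An unseen analysis plan may adjust for multiplicity.** It may. But the choice of primary endpoint and lead contrast is made in this article, and the point rests on what it fixes: several co-equal primary endpoints, one flat threshold and inconsistent contrasts.

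**Conclusion.** The concern holds in this form: two outcomes, three populations and two times are all primary at an undivided 0.05 with none leading, and the arm contrast is inconsistent between sections. The resulting error is about 26–35% for 12 separate ANOVAs and about 17–21% if the follow-up times are averaged, against a nominal 5%. These ranges depend on the assumed correlations and on the couple score being the spouses' mean.

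Two stronger conclusions are not supported. A false positive is not more likely than not under the planned ANOVAs; it passes one half only if unprotected pairwise tests are added. Nor should the power loss be put as a fall from 80% to 59%: that starts from the normal formula and ends on a t-test. Like for like, Bonferroni over three contrasts takes 80% to 66% or 76% to 59%, all on a back-solved effect. What can be said is that the stated 80% describes at most one unadjusted two-group contrast, that the article does not say which one, and that it cannot be verified from the figures given.

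**What to change.** - Name one primary test. An example that follows the stated objective is couple-level FPI total, PERMA versus IBCT, at one pre-specified follow-up time or averaged over weeks 5 and 9. Define how the couple score is formed.
- Make satisfaction, the separate analyses of women and men, and any remaining time point secondary, reported with confidence intervals.
- Report the two comparisons with control as secondary, or place them under a stated multiplicity rule.
- Make Objects, Statistical analysis and Conclusion agree with the chosen contrast.
- In Sampling and sample size, give µ1−µ2, reconcile β with power, and say that the power refers only to the single primary contrast.

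**Cost.** Only wording changes. With one primary test α stays at 0.05, and multiplicity requires no more couples. Fewer results can be called primary. The order of the contrasts is a design choice with a price: if a fixed sequence starts with PERMA versus IBCT, a non-significant first test blocks formal claims for both comparisons with control.

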### Study design 

There are two steps in this study, including developing and adjusting the content of the intervention package in step one and conducting the intervention as a randomized clinical trial in step two. The study design is shown in figure 1.

#### Step one: Developing the content of interventions' packages

Since details of counseling sessions in PERMA, IBCT, and infertility treatment training program interventions have not been reported in previous studies, especially in treating fertility problems (19, 20), the authors of the present study needed to develop and adjust a package for the content of each session for each of the three intervention groups.

Therefore, the intervention package, including the content of the sessions, the couple's responsibilities, and their homework assignments, was developed and adjusted based on a literature review (14, 21, 22) and agreement of experts in related disciplines (including reproductive health specialists, obstetricians and gynecologists, infertility fellows, a couple's therapist, a midwife and a psychologist in the Yazd Reproductive Sciences Institute). A summary of the intervention sessions is shown for the three intervention groups in tables I to III.

#### Step two: Intervention

The first group will receive the PERMA model intervention, the second group will receive the IBCT intervention, and the third group will receive an infertility treatment training program (the control group).

### Participants and setting

Participants will be couples undergoing infertility treatment at the Yazd Reproductive Sciences Institute, Yazd, Iran. This setting provides various medical and psychological facilities for couples undergoing infertility treatment. Recruitment will take place at the Yazd Reproductive Sciences Institute by the first and fourth researchers who will assess the eligibility criteria. Participants data will be kept confidential in this study.

### Inclusion criteria

The inclusion criteria will be: Iranian citizens; who are literate; have at least one smartphone and are Internet literate; have an infertility record in Yazd Reproductive Sciences Institute, Yazd, Iran; are an assisted reproductive technology (ART) candidate; and want to continue treatment at the Reproductive Sciences Institute.

### Exclusion criteria

The exclusion criteria will be: having severe fertility problems based on the FPI; having divorce documents in the courts; being a smoker or drug abuser; taking drugs for systemic diseases (except for infertility treatment drugs) according to the medical records available in the research institute; needing surgery (except for infertility surgeries); undergoing psychotherapy; having severe depression or anxiety; consulting a psychologist or psychiatrist one month or less before the study; being health care personnel; studying medical sciences, psychology, or counseling; changing residence location during the sampling period; participating in similar studies concurrently; having a problem that leads to sadness, anxiety, and depression, like the death of family members, etc. in the last two months; having a systemic disease; or being pregnant.

### Sampling and sample size

The estimated sample size is 84 husbands and wives (14 couples in each group) based on a previous study (23) and considering α = 0.05, β = 90%, power = 80% and σ = 2.5, and 15% attrition rate. The statistical formula used for sample size determination was n = 2 (z 1-
α
 / 2 + z 1 -
β
)^2^

σ

^2^ / (µ1-µ2)^2^.

In this three-arm parallel randomized clinical trial, two intervention groups (the PERMA model and IBCT) and a control group (infertility treatment training program) will be studied. 42 couples will be allocated into the three groups randomly (14 in each). Written and verbal informed consent will be obtained from husbands and wives separately.

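### The 80% power is worked out for one unnamed two-group contrast, with no printed difference and a contradictory β, so it is not established for the three-arm ANOVA that the article names

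*Protocol article*

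**What the plan says.** All references are to the protocol article.

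- **Sampling and sample size** gives 84 husbands and wives, 14 couples per group, "considering α = 0.05, β = 90%, power = 80% and σ = 2.5, and 15% attrition rate". It continues: "The statistical formula used for sample size determination was" n = 2(z at 1-α/2 + z at 1-β)²σ²/(µ1-µ2)². No value is given for µ1-µ2; the reader is referred to a previous study.
- The same section then sets out the design: "In this three-arm parallel randomized clinical trial, two intervention groups (the PERMA model and IBCT) and a control group", with 42 couples split 14 to each.
- **Statistical analysis**: "Parametric analytic statistical tests like ANOVA will be applied for the measurement of the two primary outcomes", provided the data are normally distributed, with significance at P < 0.05. Objects and Outcomes also report the scores across three study groups, for women, men and couples.
- **The contrast of interest** varies. The Introduction says "This study will aim to compare the effectiveness of the PERMA model vs. IBCT", and the Objective in the Abstract and the opening of Materials and Methods agree. The Conclusion says "the effectiveness of two psychological interventions (PERMA and IBCT) will be compared with the control group".

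**The concern.** The formula contains two means, one difference and normal quantiles, so it sizes a single comparison of two groups at a two-sided 5% level. The named analysis is a comparison of three groups. Nothing in the article says which pair of arms the formula was meant for, or that this pair is what the primary test will examine.

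The power statement also contradicts itself. Power of 80% means β = 20%, and β = 90% would mean power of 10%. If 90% was meant as 1-β, it conflicts with the 80% next to it.

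What is at stake is how the result is read. A non-significant ANOVA would be reported as coming from a trial with 80% power, although the article does not show that figure for an ANOVA. Because µ1-µ2 is missing, a reader cannot tell what size of difference the trial could be expected to detect.

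**Working it through.** **Inputs from Sampling and sample size:** two-sided α = 0.05 (the formula uses z at 1-α/2); σ = 2.5; attrition 15%; 14 couples per arm; power 80%, with 90% as the alternative reading of the β statement. **Not given:** µ1-µ2, the third mean, and whether n counts couples or persons.

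**Step 1. Can 14 per arm be reproduced?** Not directly, because µ1-µ2 is missing. With σ = 2.5 and 80% power, the formula gives 99, 44, 25, 16, 11 and 9 per arm before attrition for differences of 1, 1.5, 2, 2.5, 3 and 3.5. A base of 12 fits the printed 14: 12 × 1.15 = 13.8, rounded up to 14, and 14 × 0.85 = 11.9. (Dividing instead, 12/0.85 = 14.1 would round up to 15.) So 14 is attainable, but only with a difference that has to be assumed.

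**Step 2. Solve for the difference at n = 12.**

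µ1-µ2 = σ × √(2/n) × (z at 1-α/2 + z at 1-β)

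- At 80%: 2.5 × √(2/12) × (1.960 + 0.842) = 2.86, or 1.14 SD.
- At 90%: 2.5 × √(2/12) × (1.960 + 1.282) = 3.31, or 1.32 SD.

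**Step 3. One two-group contrast with t quantiles.** The noncentrality is (δ/σ) × √(n/2), which is 2.80 at δ = 2.86 and 3.24 at δ = 3.31. The lower figure in each row below uses the two arms only (22 df). The higher uses the three-arm error term (33 df).

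**Step 4. Three-arm F test (2 and 33 df).** The noncentrality is λ = n × Σ(µi - mean)²/σ².

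- Third arm midway, means (0, δ/2, δ): λ = n(δ/σ)²/2 = 12 × 1.144²/2 = 7.85 at δ = 2.86.
- Two arms equal, means (0, 0, δ): λ = (2/3)n(δ/σ)² = (2/3) × 12 × 1.144² = 10.47 at δ = 2.86.

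| 12 evaluable couples per arm | Formula run at 80% (δ = 2.86) | Formula run at 90% (δ = 3.31) |
|---|---|---|
| Single contrast, t quantiles | 76.4% to 77.6% | 87.2% to 88.2% |
| F test, third arm midway | 66.6% | 79.8% |
| F test, two arms equal | 79.6% | 90.3% |

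**Step 5. Sensitivity to the base (formula at 80%).**

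- If 14 couples per arm are taken as evaluable, the implied difference is 2.65. The F test has 67.3% (midway) or 80.2% (two arms equal).
- If n counted persons, with 24 per arm treated as independent (24 × 1.15 = 27.6, rounded up to 28 persons, or 14 couples), the implied difference is 2.02. The F test has 68.8% or 81.6%, and the two-sample t test 78.3%.

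The bracket hardly moves with the base. It depends mainly on the pattern of the three means and on whether 80% or 90% was used.

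**The case against.** The strongest defence is that a two-mean formula suits the stated aim. The Abstract, the Introduction and the opening of Materials and Methods all put PERMA vs IBCT first, and for that contrast at two-sided 0.05 the formula is of the right type. The only loss is from using normal instead of t quantiles at 12 per arm, which is 2 to 4 percentage points. ANOVA is introduced only as an example of a parametric test. An article may also leave contrasts and multiplicity to a fuller plan that is not shown here.

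Much of this stands. A reader might infer that the planned test definitely lacks 80% power. The article does not support that. ANOVA power needs three means, and none is printed. The F test reaches about 80% when two arms are equal. The 67% belongs to the midway pattern, the least favourable one for a given largest difference. If the formula was run at 90%, the shortfall essentially disappears.

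A reader might also infer that three unadjusted pairwise tests are planned, with an inflated error rate. The article states no such procedure, so that is not part of this point.

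What the defence does not repair is the text itself. The article never says that PERMA vs IBCT is the contrast that was sized, it names ANOVA for the primary outcomes, and its Conclusion puts the comparison with control forward. The missing difference and the β/power contradiction remain on any reading.

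**Conclusion.** The point holds as a mismatch and as an unverifiable power statement. It does not show that the sample size is wrong. The calculation covers one unnamed two-group contrast with an unprinted difference and contradictory power inputs, so the 80% is not established for the three-arm ANOVA.

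At the implied difference with 12 evaluable couples per arm, F-test power lies between about 67% and 80% if the formula was run at 80%, and between about 80% and 90% if it was run at 90%. The single PERMA vs IBCT contrast has about 76-78% or 87-88%, respectively.

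All of these figures rest on a back-solved difference, σ = 2.5 taken as printed, and an assumed base of 12. They show how far the power could be from 80%; they do not estimate its true value.

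**What to change.** Reword the two paragraphs on sample size and analysis:

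1. Name PERMA vs IBCT, the stated aim, as the primary contrast, tested at two-sided 0.05 within the three-arm model.
2. Make the two comparisons with control secondary, or test them under Holm.
3. Print µ1-µ2, and say whether n counts couples or persons.
4. Replace the β = 90%, power = 80% statement with one consistent pair.
5. Restate the power of the named contrast with t quantiles at the evaluable number. On the assumptions above this is about 78% with the three-arm error term if 80% was the target, or about 88% if 90% was.

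The 42 couples stay unchanged. The cost is rewording, a stated power that is slightly less favourable, and a secondary role for the comparisons with control.
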